### Trial outcomes and measurement

Table 2 details the trial outcomes and tools to measure them. The primary outcome is depression symptoms at endline measured as a continuous outcome. We will measure this using the PHQ-A [38]. This tool is widely used across cultures and contexts, has been adapted for and validated among adolescents in Nepal and is sensitive to change [39].

**Table 2 Tab2:** Trial outcomes and tools

Outcome type	Outcome	Tool/measure	Assessment timepoint
Primary	Depression	Patient Health Questionnaire modified for adolescents (PHQ-A)	Baseline, midline, endline, follow-up
Secondary	Functional impairment	Locally developed tool	Baseline, midline, endline, follow-up
Secondary	Anxiety	Generalised Anxiety Disorder-7 (GAD-7)	Baseline, midline, endline, follow-up
Secondary	Post-traumatic stress disorder	PTSD Checklist for DSM-5 (PCL) 8-item	Baseline, midline, endline, follow-up
Secondary	School attendance	No. of days attended in 24 days prior to baseline (excluding closures and Saturdays)	Baseline, midline, endline, follow-up
Secondary	Health-related quality of life	EuroQol-5 Dimension 5 levels (EQ-5D)	Baseline, midline, endline, follow-up
Secondary	Academic self-efficacy	Young Lives Non-Cognitive Scales	Baseline, midline, endline, follow-up
Secondary (long term)	Academic performance	Basic Education Examination School Education Examination grade	Follow-up
Secondary (long term)	School drop out	Self-report and school register	Endline and follow-up
Intermediate	Hope	Herth Hope Index	Baseline, midline, endline, follow-up
Intermediate	Emotion regulation	Difficulties in Emotion Regulation Scale (DERS-SF)	Baseline, midline, endline, follow-up
Intermediate	Self-efficacy	General Self-Efficacy Scale	Baseline, midline, endline, follow-up
Intermediate	Social support	Multidimensional Scale of Perceived Social Support (MSPSS)	Baseline, midline, endline, follow-up
Intermediate	Group cohesiveness	PM + Group Cohesiveness scale adapted for IPT	(Intervention arm only) midline, endline, follow-up
Intermediate	Interpersonal conflict	Network of Relationships Questionnaire	Baseline, midline, endline, follow-up
Predictor/moderator	School climate	Beyond Blues School Climate Scale	Baseline
Predictor/moderator	Socioeconomic status	Social and Economic Measure including household assets and food security	Baseline
Predictor/moderator	Parent mental health	General Health Questionnaire	Baseline, endline

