### Assessment and follow up

We will conduct baseline surveys with adolescents before randomisation and collect data on demographic characteristics, primary and secondary outcomes and intermediate outcomes. We will also collect data on potential predictors and moderators of intervention effects including school climate, gender norms, adversity and socioeconomic status. We will measure school climate with an abbreviated version of the Beyond Blues School Climate Scale [55] and gender norms and adversity using select items from the Johns Hopkins Global Early Adolescent Study [56]. We will collect data on indicators of wealth including household assets and food security to generate a composite indicator of socioeconomic status. We will resurvey adolescents at midline, endline and follow-up, and for longer term follow up assessments at 12-, 18- and 30-months post randomisation. Based on the pilot cRCT, we expect a 92% response rate at endline.

We will also conduct surveys at baseline with adolescents’ parents (mother or father) to collect data on potential moderators of intervention effects. We will measure parents’ mental health using the General Health Questionnaire 12-item [57], parenting behaviour with the Alabama Parenting Behaviour Scale (involvement (10 items), positive parenting (6 items) and corporal punishment (3 items) subscales) [58] and disruptive behaviour with the Disruptive Behaviour International Scale – parent report [59]. We will survey parents again at endline to collect data for an economic analysis. If the adolescent does not have a parent or the parent is unavailable for interview, this will be recorded and linked to the adolescent’s data.

All surveys will be conducted by trained research assistants using tablets programmed with data collection software. Research assistants will read the survey questions to the participant and enter their responses on the tablet. We will conduct as many surveys as possible in person. Where we cannot meet the participant in person, we will conduct the interview on the phone. In-person surveys will be conducted in a private place at the participant’s school (adolescents) or home (adolescents and parents). For phone surveys, we will arrange a time for the survey in advance. Research assistants but not participants will be masked to allocation.

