H13: For adolescents with a parent who has a mental health problem (context), through IPT they will increase their social support, normalise and validate their feelings, generate and implement solutions to their problems and reduce conflict at home (mechanism). This will offset the effect of the parent’s mental health on the adolescent’s depression (outcome).	Analysis of SSI transcripts with adolescent and parents with and without mental health problems (GHQ-12 score at baseline) and FGD transcripts with facilitators from different groups (direct and indirect probing on hypothesis)	Moderator analysis to assess if parent GHQ-12 score at baseline moderates effect of IPT on PHQ-A score at endline
Hypotheses about potential harms		
H14: For adolescents with a background of trauma (context), who recount their traumatic experiences during group sessions and to whose experiences other group members cannot relate, IPT will exacerbate their distress due to re-experiencing the stressful event (mechanism), which will result in a worsening of depression (outcome).	Analysis of SSI transcripts with adolescents with and without trauma (baseline PCL score) and FGD transcripts with facilitators from different groups (direct and indirect probing on hypothesis)	Analysis of adolescent survey data (PCL, PHQ-A outcomes)
H15: Adolescents experiencing stigma from school and community members because of their participation in IPT (context) would attend fewer sessions and the stigma would cause them distress and their depression worsens.	Analysis of SSI transcripts with adolescents who have experienced stigma and facilitator FGD transcripts	Cross-sectional analysis of adolescent survey data (endline, questions about experience of stigma due to participation in IPT, PHQ-A
H16: In groups adolescents are encouraged to generate and select solutions to solve their interpersonal problems. If the group is poorly facilitated these solutions may run counter to our theory of change and could cause adolescents harm for example by inciting violence in the context of a dispute. This could exacerbate adolescents’ depressive symptoms.	Analysis of SSI transcripts with adolescents and facilitator FGD transcripts probing on the nature of solutions generated within groups and their consequences Analysis of information from facilitator session and supervision notes on solutions and consequences	We will not have quantitative data to test this hypothesis.

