To estimate indirect costs for the modified societal perspective, we will document productivity loss and informal care costs by recording adolescents’ time spent on intervention-related activities (including travel and participation) if relevant, as well as time and costs associated with outside healthcare utilisation. At endline and follow-up, we will collect data on adolescent health care visits since the baseline survey, including the time and out-of-pocket expense for each visit (across a range of non-school based formal and informal healthcare types available locally). For each type of healthcare service received, we will establish whether its cost is fully covered by out-of-pocket expenditures, or whether it was partially or fully subsidised by the provider. We will record the estimated subsidised cost of services using publicly available information; if subsidised costs are not available, we will contact service providers to establish appropriate estimates or ranges which will be tested in sensitivity analyses. We will collect productivity and informal care costs from interviews with all available parents at endline and follow-up, documenting the time parents have spent providing care as well as opportunity costs of care-seeking for both parents and adolescents. Adolescents will be asked about any earnings from paid work and opportunity costs of healthcare utilisation at midline, endline, and all follow-up surveys. Intervention participants will also be asked about opportunity costs of IPT attendance at midline and endline during group cohesion assessments to maintain masking of group allocation. Cost data will be collected prospectively throughout the trial in Nepali rupees (NPR) and reported in 2024 prices.

The primary health outcome of interest for the economic evaluation analyses is the quality-adjusted life year (QALY). QALYs will be calculated using EQ-5D-5 L health utility scores from adolescents at each planned timepoint for data collection. Using this data, we will derive QALY weights using existing value sets from India, which represent the closest cultural context for which EQ-5D-5 L value sets are available [65].

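### As written, H15 places questions on stigma from taking part in IPT in the endline survey that carries the primary PHQ-A, which is likely to reveal the arm to research assistants who are meant to be masked

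*Protocol article*

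**What the plan says.** The relevant statements are spread over several sections of the protocol article.

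- **Table 4, H15** (Mechanisms of change and contextual factors). The hypothesis is that adolescents who meet stigma because they take part in IPT will attend less and become more depressed. Its quantitative source is "Cross-sectional analysis of adolescent survey data (endline, questions about experience of stigma due to participation in IPT, PHQ-A".
- **Trial outcomes and measurement.** "The primary outcome is depression symptoms at endline measured as a continuous outcome", using the PHQ-A; endline is 17 weeks after randomisation.
- **Assessment and follow up.** "All surveys will be conducted by trained research assistants using tablets programmed with data collection software". On mode: "Research assistants will read the survey questions to the participant and enter their responses on the tablet". On masking: "Research assistants but not participants will be masked to allocation".
- **Economic evaluation data collection.** Intervention participants are asked about "opportunity costs of IPT attendance at midline and endline during group cohesion assessments to maintain masking of group allocation".
- **Tables 2 and 3.** Table 2 restricts the group cohesion measure to the intervention arm. Table 3 lists the cohesion assessment separately from the adolescent surveys. It also lists an IPT treatment satisfaction survey for intervention participants, which the Implementation section says is given in the last group session.
- **Study design; Power and sample size.** Schools are the unit of allocation, with 10 to 16 participants each.
- **Discussion.** Masking of research assistants is named among the strengths, as a protection against detection bias.

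**The concern.** Three statements do not fit together: the stigma items are endline adolescent survey data, masked assistants read that survey aloud, and IPT-specific questions have to be kept out of it to preserve masking. The article states the third principle itself for the opportunity-cost items, but H15 does not follow it.

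The primary outcome is a symptom scale read aloud by an interviewer to participants who know their arm. Masking the interviewer cannot remove bias from the participant's own knowledge. It can limit what the interviewer adds through tone, prompting or the recording of unclear answers. If the interviewer can tell the arm, that protection is weakened at the primary endpoint, and the strength claimed in the Discussion is no longer fully earned.

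**Working it through.** **1. Does the item reveal the arm?** There are two ways to ask it in the survey.
- Shown only to intervention participants: its appearance on the tablet gives the arm away.
- Asked of everyone: only intervention participants have taken part in IPT, so the answers are likely to give the arm away.

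Stigma questions worded so that they apply equally in both arms would not have this effect, but H15 ties its questions to participation in IPT.

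**2. Could H15 mean the cohesion assessment?** H8 and H10 in the same table name group cohesion data when they use it. H15 names the adolescent survey. The table therefore distinguishes the sources, and the plain reading of H15 is the survey.

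**3. Would asking the PHQ-A first be enough?** Only partly, because all participants in a school share an arm. Let m be the participants per school (10 to 16, from Power and sample size) and k the number of assistants covering it, each knowing only their own interviews. Suppose the PHQ-A comes first and each assistant's first interview discloses the arm. The share of interviews held after disclosure is (m − k)/m.
- k = 1: 9/10 = 90% to 15/16 = 94%.
- k = 4: 6/10 = 60% to 12/16 = 75%.

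Both k and the item order are assumptions; the article gives neither. An assistant who returned to the school at 32 weeks would already know its arm.

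**4. What could a bias do?** The article gives no interviewer effect, so this is illustration only. The Mediation analysis section gives an effective sample size of 308 at ICC 0.07 and 8% missingness (46 × 12 / 1.79 = 308). For two equal arms in SD units, SE = 2/√308 = 0.114. Let b be the average bias across the whole arm comparison when there is no true effect. The two-sided rejection rate at nominal 5% is Φ(−1.96 + b/SE) + Φ(−1.96 − b/SE).
- b = 0.05 SD (0.05 × 3.05 = 0.15 PHQ-A points): b/SE = 0.439, rate about 7%.
- b = 0.1 SD (0.1 × 3.05 = 0.3 points): b/SE = 0.877, rate about 14%.

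With the article's effective size of 412 (ICC 0.03), SE = 2/√412 = 0.099, and b = 0.1 SD gives about 17%.

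**The case against.** The strongest reply is that a cell in a hypothesis table says which data will be analysed together, not how a form is laid out. The article does not say who asks the stigma items, in what order or in what wording, and the cell ends with an open bracket, so it may be cut short. Two intervention-only instruments exist at endline, the cohesion assessment and the treatment satisfaction survey. Either could hold the items and be linked to the PHQ-A afterwards. The handling of the opportunity-cost items shows that the team knows the risk and may have treated the stigma items in the same way. Form layout is also something a condensed article often leaves out.

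Much of this stands, and it limits what can be concluded. A reader might infer that masking has failed at the primary endpoint; the article does not show that. A reader might also infer that one interview unmasks all 10 to 16 participants of a school. That is an upper bound: interviews already done are unaffected if the PHQ-A came first, and assistants who have not heard an answer stay masked. The 14% is not an estimate for this trial. Nor is assessor masking the only issue. The Discussion concedes that participants are unmasked, and arm could leak in other ways: Table 1 describes a film about IPT shown in intervention schools, and parents who joined a pre-group session are surveyed at endline.

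The reply does not remove the conflict in the text. H15 names a source, that source is the masked survey, and the safeguard stated elsewhere is not stated here. This is an inconsistency in what is written, not a missing detail.

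**Conclusion.** The point holds in a limited form. Followed as written, H15 would put IPT-specific items in the masked outcome survey. That conflicts with the masking statement under Assessment and follow up, with the strength claimed in the Discussion, and with the safeguard applied to the opportunity-cost items. The likely consequence is that some assistants learn a school's arm during the endline interviews and carry that knowledge into later interviews there and at 32 weeks.

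How many interviews are affected depends on item order and on the number of assistants per school, neither of which is stated. The size and direction of any resulting bias cannot be derived from the document. The false-positive rates above rest on assumed biases and show only why the matter deserves attention. If the items are in fact asked in an intervention-only instrument, the remedy shrinks to correcting the H15 entry and confirming that the instrument is kept apart from the masked survey.

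**What to change.** - Collect the IPT-stigma items in an existing intervention-only instrument, separate from the masked outcome survey: the group cohesion assessment, as for the opportunity-cost items, or the treatment satisfaction survey. The latter is given in the last group session and H15 itself predicts lower attendance among stigmatised adolescents, so it may miss some of those the hypothesis concerns.
- If research assistants administer that instrument, schedule it after the school's PHQ-A interviews are complete, where existing staffing allows.
- Amend the H15 data source in Table 4 to match.
- Flag any wave already surveyed with these items and examine it in a sensitivity analysis of the primary outcome. Waves 1 and 2 began IPT in June and July 2025, so their endline may already have passed.
- If the items stay in the survey, qualify the masking statements under Assessment and follow up and in the Discussion.

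The cost is small: a few items moved between questionnaires already in use, a tablet form update for the remaining waves (recruitment is expected to run to 30 November 2026), and a line in Table 4. Scheduling the instrument after the outcome interviews may need extra visits. A separate assessor would need extra staff, so it is an option and not a condition. The change removes one route to unmasking and does not by itself guarantee masking.

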### Economic evaluation data collection

We will primarily adopt a provider perspective for the economic evaluation; secondarily, we will adopt a modified societal perspective to additionally account for the out-of-pocket costs and opportunity costs to adolescents and caregivers related to adolescents’ healthcare utilisation. To estimate the costs of the intervention and control conditions incurred by the implementing agency, monthly project budget actuals will be entered in an Excel tool by TPO Nepal staff members and continuously updated throughout the trial. We will divide costs into start-up or implementation costs and allocate them to different cost centres and intervention activities by trial arm. Major expected cost categories for both intervention and control groups include *personnel*,* equipment*,* travel*,* supervision and monitoring*, and *finance and administration.* TPO Nepal staff members will allocate staff salaries between trial arms; identify relevant costs incurred during the pilot which also contribute to the full trial cost; and document use of facilities and supplies in both Chitwan and Kathmandu office locations.

To estimate indirect costs for the modified societal perspective, we will document productivity loss and informal care costs by recording adolescents’ time spent on intervention-related activities (including travel and participation) if relevant, as well as time and costs associated with outside healthcare utilisation. At endline and follow-up, we will collect data on adolescent health care visits since the baseline survey, including the time and out-of-pocket expense for each visit (across a range of non-school based formal and informal healthcare types available locally). For each type of healthcare service received, we will establish whether its cost is fully covered by out-of-pocket expenditures, or whether it was partially or fully subsidised by the provider. We will record the estimated subsidised cost of services using publicly available information; if subsidised costs are not available, we will contact service providers to establish appropriate estimates or ranges which will be tested in sensitivity analyses. We will collect productivity and informal care costs from interviews with all available parents at endline and follow-up, documenting the time parents have spent providing care as well as opportunity costs of care-seeking for both parents and adolescents. Adolescents will be asked about any earnings from paid work and opportunity costs of healthcare utilisation at midline, endline, and all follow-up surveys. Intervention participants will also be asked about opportunity costs of IPT attendance at midline and endline during group cohesion assessments to maintain masking of group allocation. Cost data will be collected prospectively throughout the trial in Nepali rupees (NPR) and reported in 2024 prices.

The primary health outcome of interest for the economic evaluation analyses is the quality-adjusted life year (QALY). QALYs will be calculated using EQ-5D-5 L health utility scores from adolescents at each planned timepoint for data collection. Using this data, we will derive QALY weights using existing value sets from India, which represent the closest cultural context for which EQ-5D-5 L value sets are available [65].

### Power and sample size

#### Primary analysis

The aim of the primary analysis is to test the overall impact of IPT on adolescent depressive symptoms compared to enhanced usual care through a two-armed cluster RCT with secondary schools as the unit of randomisation. To fulfil the study objectives, we plan to recruit 48 schools, with 24 schools per arm with 10 to 16 adolescents per school taking part, giving a range of 480 to 768 adolescent individuals taking part. As the sample size is fixed due to logistics, we will take the approach of estimating the effect which can be detected by our cluster randomised design. For the purpose of sample size calculation, we will need the intraclass correlation coefficient (ICC, the proportion of variation due to variation between clusters), the standard deviation of the depression measure, the arithmetic mean of the cluster size, the standard deviation of cluster size variation in order to calculate the coefficient of variation for cluster size (cluster SD/cluster mean), the number of clusters, desired power, alpha level, direction of test (here two-way) and the rate of dropout of schools and adolescents. This information will allow us to use clustersampsi, a stata module for cluster randomised trial power analysis.

We use the baseline standard deviation of included adolescents from the pilot trial PHQ-A, which is 3.05. Assuming the distribution of clusters is uniform across the 10 to 16 range, with an arithmetic mean of 13 and standard deviation of 1.97, results in a coefficient of variation for cluster size of 0.151. However, in the pilot study 12/161 (8%) of adolescents dropped out by endline (the primary endpoint), which would approximate one adolescent per cluster. Here we’ll assume both 8% and a more conservative drop-out of two per cluster giving an additional missingness rate at individual level of 15%. No schools dropped out in the pilot study, but we will also assume one school in each group will be lost to follow-up. This leaves us with 46 schools with an average of 12 or 11 per cluster and coefficients of variation of 0.16 and 0.181 respectively. We use both a conservative ICC of 0.07 for the PHQ-A based on data collected on symptoms of depression using the Depression Self Rating Scale during the IPT feasibility study [19], and a more liberal value of 0.03 as ranges from 0.05 to 0.01 are more typical in community interventions. Finally, we assume a two-way test with 90% power and alpha set to 0.05. Given these parameters the smallest detectable effect size at the primary outcome timepoint at 8% missingness and ICC = 0.07 would be 0.29 (0.3 at 15% missingness) and the design effect (the effective reduction in sample size) due to clustering 1.79 (1.73 at 15% missingness). For an ICC of 0.03, the smallest detectable effect size would be 0.25 at 8% missingness and 0.26 at 15% missingness (design effects DE of 1.34 and 1.31 respectively). Hence, the study is well powered to detect small to moderate effects. These standardized effect sizes correspond to group difference 0.9 or less on the PHQ-A scale.

